### Other non-pharmacological therapeutic measures and Patient Compliance

During the intervention period, other non-pharmacological therapeutic measures which differ from those stated in the intervention design will be advised against. However, in the case of non-pharmacological therapeutic measures occurring, they will be registered and included in the analysis.

In the follow-up visits at 3, 6 and 12 months, we will ask about the patient compliance of recommendations of treatment and the questionnaires will be completed. Furthermore, if the patient is unable to attend the follow-up visits, the data collection will be carried out by telephone call.

Compliance to the group sessions will be assessed by registering the number of group sessions that patients attend.

To ensure patients' adherence to the group sessions, they will be asked a time preference (morning or afternoon) to attend the sessions. One week prior to the group session, they will receive a phone call to report the date, time and location of the session and on the day before, an SMS message with the same information will be sent.

At the end of the study, the control group will receive the compact disc of Jacobson's progressive relaxation technique, the educational booklet "The Back Manual" and the audiovisual.

### Outcomes

Primary outcomes are:

- *Change in disability measured by Roland Morris disability questionnaire (RDQ) *[20,21]. The primary outcome is change in the score on the Roland and Morris disability questionnaire at three months after onset of pain.

Our study will use the Spanish version of the questionnaire, trans-culturally adapted and validated by the Kovacs Foundation, in collaboration with a team of researchers from various hospitals, including the Kovacs Foundation and different PHCCs. Conducted studies demonstrate the *RDQ *questionnaire is a reliable and sensitive measure to evaluate the disability which LBP may generate, namely the limitations in daily tasks which it may entail. Furthermore, the RDQ questionnaire may perform better in the general population [22]. Total scores are obtained through addition of scores for each selected statement, rating from 0 to 24.

- *Intensity of Pain assessed by Pain Questionnaire Spanish version (Mc Gill Pain Questionnaire, (Melzac, 1975) *[23-27], This is a self-administered questionnaire. It is based on the view of pain perception as multidimensional: sensory-discriminative, motivational-affective and cognitive-evaluative. It rapidly identifies the predominant components of pain perceived by the patients. It covers 62 descriptors distributed along 15 classes and 3 dimensions (sensorial, affective and evaluative). It assesses 3 parameters: Total Intensity score, Current Intensity score and Visual Analogical Scale (VAS). Total Intensity score is obtained by adding each class score. Each class score is obtained from ticking one or none of the descriptors in each class. If one is ticked, it scores 1, and if none are ticked, it scores 0. Total Intensity score, which will be located between 0-14, is obtained by adding these three dimensions. Current Intensity score is obtained from a scale such as Likert, rating from 0 to 5. Analogical Visual Scale rates from 0 to 10.

- *Quality of Life measured by SF-12*. We will use the Spanish version of SF-12 because for large group studies, the differences in measurement reliability between the SF-12 and SF-36 are not as important and the SF-12 is worthwhile for specific populations based on large sample sizes [28]. The 12 items provide a representative sampling of the content of the 8 health concepts and operational definitions of those concepts, including what respondents are able to do, how they feel, and how they evaluate their health status. The dimensions were physical function (2 items), physical role (2), social functioning (1), emotional health (2), mental health (2), vitality (1), bodily pain (1), general health (1). The answer options on the Likert scale evaluate the intensity and frequency of these dimensions. Time reference in the version used is 4 weeks. Scores rate from 0 for worse health status to 100 for best health status, for each of the dimensions. The questionnaire should preferably be self-administered.

Secondary outcomes are:

- *Duration of the current episode of LBP (pre-study and study duration)*. We will consider the current episode finished when the pain and its impact on the person's daily life is reduced, even when the pain cannot be cured completely [29].

- *Work sick leave (yes or no)*

- *Duration in days of work sick leave*

- *Percentage of change in pharmacological treatments*.

- *Wrong beliefs, inadequate behaviour and work factors assessed by Fear Avoidance Beliefs Questionnaire (FAB) *[30]. Among psychosocial factors associated with LBP, avoidance behaviour of physical activity or work due to fear of pain have been demonstrated to have an influence on the disability. The Spanish version of the FAB questionnaire allows us to quantify beliefs and fears regarding the causes and consequences of pain, with validity and accuracy in patients with LBP. This questionnaire, recently validated, contains 16 statements (five related to physical activity and eleven to work activity), which patients score from 0 to 6 depending on their degree of agreement or disagreement. Thus, higher scores indicate a higher degree of avoidance behaviour. Completion takes around ten minutes and it can be self-administered.

- *Anxiety and Depression measured by The Spanish version of the Goldberg questionnaire, the "Escala Ansiedad y Depresión de Goldberg" (E.A.D.G) *[31]. This was designed to aid GPs and other non-psychiatrists in the better recognition of mental illness. Its validity and discriminatory power for detecting anxiety and depression has been demonstrated, as well as its usefulness as an interview guideline. Each scale has 9 items. The anxiety scale has 4 core symptoms (keyed up, worrying a lot, irritability and difficulty relaxing) and 5 supplementary symptoms (insomnia, headaches, autonomic symptoms, health worries and delayed sleep). The depression scale has 4 core symptoms (low energy, loss of interest, loss of confidence and hopelessness) and supplementary symptoms (inefficient thinking, poor appetite/weight loss, early waking, feeling sluggish and feeling worse in the morning). The interpretation is made by adding the anxiety score to the depression score. Patients with anxiety scores of five or depression scores of two have a 50% chance of having a clinically important disturbance.

- *Satisfaction with care *will be measured with VAS scale ranging from 0 to 10.

- *Patient's assessment of global perceived effect *will be measured by self-assessment on a 7-point scale [32].

### Other variables

The main independent variable is the intervention arm: biopsychosocial multidisciplinary group intervention, or usual clinical care.

The following socio-demographic variables will be recorded: age; sex; educational level (illiterate or non-completed primary studies, completed primary studies, second degree studies, university studies); working situation (housewife, self-employed, employed elsewhere); profession; number of children or other relatives to care for; marital status. Clinical variables: weight and height; previous non-specific acute or sub-acute LBP episodes (none, one or two, three or more); pre-study duration of the current episode of LBP; pain irradiation to the leg (yes or no); severity of pain irradiated to the leg (analogical visual scale); stretching radicular test-Lasegue's maneuver (it has not been carried out, positive if onset of pain irradiated to the leg appears below 30° or between 30-60°, is negative if this pain appears upon 60° or does not appear); prescribed pharmacological treatment: muscle relaxants, analgesics, AINEs, corticoids, ansiolitic drugs, gastric protectors, prescribed diagnostic tests: radiography, Nuclear Magnetic Resonance, Scanner; patient compliance of recommendations and treatments; referrals to other departments (Orthopaedics, Rehabilitation, Neurosurgery, other); Primary Health Care and Hospital emergency visits due to current sub-acute LBP episode; non pharmacological therapeutic measure (relaxation, physiotherapy, reflexology, psychotherapist, etc); vigorous physical activity [33].

### Data collection and follow-up

All the outcomes will be measured at the individual level. All participants will be invited to attend the PHCC for outcome assessments. They will be assessed on his/her first visit to the PHCC, and at 3 months, 6 months, and 12 months after the onset of LBP. The timing for the second assessment was chosen because it would detect the patients' situation near the point at which they would become chronic. The timing for the last assessment was chosen because adequate follow-up time has been recommended by many authors[6,13]

At each assessment, an expert trained fellow (a psychologist) will make up to three phone calls at different times during the day to make the appointments. During the visit, he/she will fill out the questionnaires by interviewing the participant, will do Lasegue's maneuvre test, will collect information by reviewing medical records, will contact the patient's GP to inquire about their development (compliance of treatment, sick leave, evolution to chronic back pain) and will resolve any questions about the conduct of research.

On January 2009, a pilot study was carried out. Its completion with 14 participants allowed us to: discuss the inclusion and exclusion criteria and the questionnaires used (length, understanding and acceptance): plan the recruitment of patients to achieve a suitable number of participants per group (5 out of 7 invited to participate, attended); redefine the length and distribution of the contents of the intervention and assess adherence to the intervention.

The recruitment period is six months.

Table 4 gives an overview of data collection. Data were entered in a centralised database by the expert trained fellow and the quality of the data will be revised. Figure 1 shows the trial flow chart of the study.

**Figure 1 F1:**
[figure not shown]
**Study flow chart**. Notes: PHCC = Primary Health Care Centres; GP = General practitioner.

**Table 4 T4:** Overview of data collection

	*Baseline*	*Follow-up*		
**Outcome Measures**	**15 days after onset of LBP**	**3 months**	**6 months**	**12 months**

Disability: Roland Morris Questionnaire (RDQ)	X	X	X	X

McGill Pain Questionnaire	X	X	X	X

Quality of life Questionnaire (SF-12v2)	X	X	X	X

Duration of the current episode LBP	X	X	X	X

Work sick leave (yes or no)	X	X	X	X

Duration of work sick leave in days	X	X	X	X

Percentage of change in pharmacological treatments	X	X	X	X

Fear Avoidance Beliefs Questionnaire (FAB)	X	X		X

Goldberg Scale (Anxiety and Depression) Questionnaire	X	X		X

Satisfaction with care	X	X	X	X

Patients' perceived global assessment	X	X	X	X

***Independent Variables***				

***Socio-demographic***				

Age, sex, educational level, work situation, profession, number of children, marital status	X			

***Clinical***				

Weight and height	X			X

Previous LBP episodes	X			

Pre-study duration of the current episode of LBP	X			

Pain irradiation to the leg	X			

Severity of the pain irradiated to the leg (VAS)	X			

Stretching radicular test-Lasegue's Maneuver	X			

Prescribed pharmacological treatment	X	X	X	X

Prescribed diagnostic tests: Rx, NMR, Scanner	X	X	X	X

Patient compliance of recommendations-treatment	X	X	X	X

Referrals to other services	X	X	X	X

Primary Health Care and Hospitals emergency visits	X	X	X	X

Non pharmacological therapeutic measures*	X	X	X	X

Vigorous Physical Activity Questionnaire	X	X	X	X

Notes: LBP = Low back pain; VAS = Visual Analog Scale; Rx = Radiography; NMR = Nuclear Magnetic Resonance

* Non pharmacological therapeutic measures such as relaxation, physiotherapy, reflexology, psychotherapist or others

### Sample size

The sample-size calculation is based on change in RDQ at three months after onset of LBP. It is recommended that a change in 2 to 3 points on the RDQ should be considered the minimum clinically important change [22]. To allow for the cluster randomisation by PHCC, we assume an intraclass correlation coefficient of 0.1 [34] and a minimum average number of individuals sampled per PHCC of 25. In order to detect a difference of 2.5 points between the two intervention arms with a standard deviation of 5.7 [22,35], an alpha error of 0.05, a beta error of 0.10, and a 20% dropout rate, a sample size of 932 subjects was required, 466 subjects per intervention arm. Therefore, the total number of PHCCs is 38 (19 for group).

### Statistical Analysis

Data will be analysed in accordance with CONSORT guidelines, extension to cluster randomised trial. Data will be analysed by intention-to-treat. To address potential biases due to incomplete follow-up, we will analyse patients with complete data at all time points and those with data at any time point, using the last known value carried forward to replace missing values. Bias due to non-response will be assessed at each follow-up.

The primary end points for the trial will be 3 months (short term), 6 months and 12 months (long term).

We will obtain descriptive statistics for the outcome measures, baseline characteristics and clinical measures as mean (standard deviation) or numbers (percentages), with 95% confidence intervals at each assessment for all the patients and for each group.

The distribution of data will be checked to ensure that parametric assumptions are met, and non-parametric analyses will be used when appropriate. We will use independent *t *tests or Mann-Whitney U tests for continuous data and Χ^2 ^tests or Fisher's exact probability test for categorical data for unadjusted comparisons between groups at each assessment.

Continuous data for change in scores from baseline will be compared between groups and for each group. The paired t-test for difference will be used to compare the change between pre- and post- intervention.

To decide on an important change in individuals, we will contrast the distributions of changes in all the questionnaires and in each assessment, in individuals who change to chronic state and in individuals who do not [22]. We will do the same between those individuals who return to work and those who do not. We will compare individual change scores to the standard error of measurement (SEM).

To detect changes in groups, the intervention effect will be calculated through the effect-size for each questionnaire and at each assessment. Effect-size was calculated following the method of Kazis et al [36]

We will evaluate responsiveness of each scale by standardised response mean (SRM) [37] and receiver-operating characteristic method (ROC curve). The SRM will be performed between two-time points (baseline and each assessment) and for each intervention arm. We have chosen recovery according to the patient as an external criterion for clinically relevant improvement.

Simple correlations between the scores of the different scales (disability, severity of pain, quality of life and psychosocial scales) will be obtained through the Pearson linear correlation coefficient or the Spearman correlation, in the case of parametric assumptions not being met, at each assessment.

Since the unit of randomisation is the PHCC, we will use a regression analysis of individual level data using methods for clustered data [38]. For adjusting comparisons and to account for cluster randomisation, multilevel linear regression analyses on repeated measures on each of the outcome scales will be used to assess the effect of intervention and to investigate the factors that influence each of the outcome scales at each time point adjusting for baseline scores, baseline characteristics of patients (socio-demographic, clinical and professional) and the other scale scores if they are found to affect outcomes significantly over time. The possible association between intervention and time will be studied. The PHCC and the individual will be considered as random effects and intervention and time as fixed effects.

A multilevel Cox regression model will be used to evaluate the association between the main independent variable, the prognostic factors and the time of subsiding of the current episode of LBP or return to work at 3 months. The patients for whom the duration of the current episode is more than 3 months or those who do not return to work at 3 months will be censored at that time. Kaplan-Meier survival curves will be used to compare the rate of evolution to chronicity and return to work between both groups. Logrank and Breslow test will be used for testing the equality of survival among groups.

The differences in medication prescription at baseline and at each assessment in the interventions and control groups will be compared.

We will calculate the relative risk reduction (RRR) and number needed to treat (NNT) to facilitate development of clinical guidelines for future management.

We will study the interactions and the collinearity. The collinearity of the maximal models will be evaluated using the criteria proposed by Belsley [39]. The significance level of all models will be set at 5%.

The SPSS statistical package for Windows, version 17 (SPSS Inc., Chicago, IL) and the SAS 9.1.3 for Windows (SAS Institute Inc., Cary, NC, USA), will be used for statistical analysis.

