## Background

Low back pain (LBP), in any of its forms (acute, sub-acute or chronic), is a common and important reason for consultation with the general practitioner (GP). The point prevalence rate of LBP has been estimated as 14.8% in a study carried out in the general Spanish population [1], while the same study finds a probability of 44.8% of presenting at least one episode of LBP in a period of six months, similar to the annual prevalence of 41% observed in the Dutch population [2,3].

LBP has an important impact on the performance of daily tasks in individuals who present the condition and on their quality of life. It also has family and social repercussions, which are often ignored [1,3]. It is one of the most frequent causes of absenteeism, estimated at an average of 21.9 days of work sick leave per episode [4]. However, most data related to daily activity come from the field of work and exclude relevant groups such as housewives; thus the consequences of this problem are clearly underestimated [1].

A study carried out in 36 Primary Health Care Centres (PHCC) in Spain describes the management of a patient with non-specific LBP. Courses of action taken include: 98% of the patients receive pharmacological treatment, 19% some kind of physical therapy and 10% are referred to surgery, while 43% of the patients are assessed through radiological techniques. This study showed that, although management of the patients is consistent with the recommendations based on evidence, after two months of treatment, the pain continued in 37% and had worsened in 10% of patients [5].

Multi-causality of LBP limits, in some cases, the election of an approach strategy which improves symptomatology and obtains effective results. Little is known about effectiveness of primary prevention, both in the general population and in the work place. A systematic revision undertaken by Linton et al [6], observed that physical exercise alone showed a weak, though consistent, preventive effect. However, the US Preventive Services Task Force [7] does not find sufficient evidence to support the recommendation for or against postural exercises or modification of risk factors to prevent LBP.

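### Missing outcomes are handled only by complete cases and last value carried forward; at the 3-month primary outcome the carried value is baseline, so LOCF dilutes a real effect under equal dropout and can create a false one under unequal dropout

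*Protocol article*

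**What the plan says.** The Statistical Analysis section promises an intention-to-treat analysis. To deal with bias from incomplete follow-up it then states: "we will analyse patients with complete data at all time points and those with data at any time point", the second set being completed by "using the last known value carried forward to replace missing values". It adds that "Bias due to non-response will be assessed at each follow-up", but attaches no method or alternative estimate to that.

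Later in the same section, "multilevel linear regression analyses on repeated measures on each of the outcome scales will be used" to assess the intervention, adjusting for baseline score, with centre and individual as random effects. The text does not say whether this model is fitted to the filled data, to the complete cases or to the observed values.

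The primary outcome is change in Roland Morris score at three months after onset (Outcomes). Table 4 shows nothing measured between baseline and that visit. The Sample size section allows for "a 20% dropout rate", one rate with no split by arm.

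**The concern.** LOCF assumes that a patient who is lost stays at the last recorded value. For the 3-month outcome that value can only be baseline, so the imputed change is exactly zero.

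The article's own account of the condition makes this a poor assumption. The Background cites a Spanish primary care study in which, "after two months of treatment, the pain continued in 37% and had worsened in 10% of patients". That leaves 53% to 63% whose pain did not continue, depending on whether the 10% lies inside the 37%. The Discussion says that about 6% to 10% recur or become chronic. It also links attendance to being in pain, so some of those lost may be the ones who recovered.

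The primary estimate would then depend partly on who was lost. Under equal dropout a real effect is diluted. Under unequal dropout the natural improvement, which is common to both arms, no longer cancels.

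The complete-at-all-times set has a different weakness. A patient seen at 3 months but not at 12 is removed from the 3-month analysis. This conflicts with the stated intention-to-treat principle, and it gives bias if completeness depends on the course of pain beyond what the baseline covariates explain.

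**Working it through.** **Inputs from the Sample size section.** Difference 2.5, SD 5.7, alpha 0.05 (two-sided reproduces the stated number), power 90%, intraclass correlation 0.1, 25 patients per centre, 20% dropout, 466 per arm.

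**Inputs assumed, because the article does not give them.** Mean control improvement g, and dropout by arm (dI intervention, dC control).

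**1. The plan's own figure.** Patients per arm before inflation: 2 × (5.7 × (1.960 + 1.282) / 2.5)² = 109.2, rounded up to 110. Design effect: 1 + (25 − 1) × 0.1 = 3.4. Per arm: 109.2 × 3.4 / 0.8 = 464, or 110 × 3.4 / 0.8 = 467.5, against 466 stated. The calculation reproduces. With 466 × 0.8 = 373 observed per arm, power for 2.5 points is 90.1%.

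**2. Expected 3-month difference under LOCF.** Patients lost score zero change. If loss is otherwise unrelated to outcome and the true effect is δ:

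E = (1 − dI)(g + δ) − (1 − dC)g = (1 − dI)δ + g(dC − dI)

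**3. Equal 20% dropout.** The second term vanishes: E = 0.8 × 2.5 = 2.0, whatever g is. LOCF counts all 466 per arm, so SE = 5.7 × √(2 × 3.4 / 466) = 0.69, and power = Φ(2.0/0.689 − 1.96) = about 83%. The design effect is held at 3.4, as in the plan.

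The added zeros do not much change the SD. With g = 5, the arm variances are 0.8 × 5.7² + 0.16 × 5² and 0.8 × 5.7² + 0.16 × 7.5². The SDs are about 5.5 and 5.9, so the pooled value stays near 5.7.

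**4. Unequal dropout with no true effect.** E = g(dC − dI). For a 10-point gap, such as 15% v 25%:

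| Assumed g | False difference | Rejection rate at nominal 5% (SE 0.69) |
|---|---|---|
| 3 | 0.3 | about 7% |
| 5 | 0.5 | about 11% |
| 7 | 0.7 | about 17% |

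**5. Unequal dropout with a true 2.5-point effect.**

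| Assumed g | 25% intervention, 15% control | 15% intervention, 25% control |
|---|---|---|
| 3 | 0.75 × 5.5 − 0.85 × 3 = 1.58 | 0.85 × 5.5 − 0.75 × 3 = 2.43 |
| 5 | 0.75 × 7.5 − 0.85 × 5 = 1.38 | 0.85 × 7.5 − 0.75 × 5 = 2.63 |
| 7 | 0.75 × 9.5 − 0.85 × 7 = 1.18 | 0.85 × 9.5 − 0.75 × 7 = 2.83 |

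LOCF inflates the effect when g(dC − dI) exceeds dI × δ. With 15% intervention dropout that threshold is 0.15 × 2.5 = 0.375, reached at g = 5 and 7 but not at 3.

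**6. Whether an observed-data analysis does better.** A large-sample simulation used one follow-up and no clustering. It assumed baseline mean 10 and SD 5, control improvement of 4 or 6 points, and dropout of about 20% that depended on baseline in opposite directions in the two arms, which is a demanding case.

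| Analysis | True effect 2.5 | True effect 0 |
|---|---|---|
| Observed data, baseline-adjusted | 2.5 | 0.0 |
| LOCF, unadjusted | 1.4 | −0.6 |
| Complete cases, unadjusted | 1.8 | −0.7 |

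Here the gain over complete cases comes from baseline adjustment. With several visits, the repeated-measures model also keeps patients with partial follow-up.

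**The case against.** Several points on the other side stand.

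- A reader might infer that both methods shrink the effect. They do not: dilution belongs to LOCF. Complete cases are unbiased if loss is unrelated to outcome, and also if loss depends only on baseline variables that the model adjusts for. Nor does LOCF always shrink, as step 5 shows.
- A reader might infer from the 10 hours of group sessions that dropout will differ by arm. The article does not say so. Missing a session is non-adherence, which is recorded separately. Outcomes in both arms are collected by a trained fellow with up to three calls to arrange each visit, by telephone if the visit is missed, and with recall mechanisms. Unequal loss is plausible, but it remains an assumption.
- A reader might put power under LOCF lower still, by pairing the diluted 2.0 points with the standard error for the 373 observed patients per arm. LOCF counts all 466, so about 83% is the consistent figure.
- The 37% concerns persistence of pain, not Roland Morris score, in patients not selected for pain already lasting 15 days to 12 weeks. Follow-up is timed from onset, so a late entrant has little time to improve before three months. Mean improvement could be small, and the false differences in step 4 all lie below the 2 to 3 points that the article calls clinically important.
- The article does not rank LOCF as the main analysis, and a baseline-adjusted model gains nothing from a patient with no follow-up value.

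None of this changes the stated rule. Better collection reduces the number missing but not how they are scored. Assessing non-response produces no corrected estimate. The dilution in step 3 needs no assumption about natural improvement or unequal loss.

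**Conclusion.** The point holds. The article fixes two ways of handling missing outcomes, and one of them biases the primary 3-month comparison. The firmest figure is the fall from 2.5 to 2.0 points, with power about 83% instead of 90%. It rests on the planned 20% dropout being equal by arm and unrelated to outcome, on SD 5.7 and design effect 3.4, and on baseline-only patients counting as having data at any time point, which the wording leaves open.

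The false-positive figures rest further on an assumed 10-point dropout gap and assumed mean improvement of 3 to 7 points. The direction of the bias under a true effect depends on which arm loses more patients. At 6 and 12 months a later value may be carried, so the bias there is probably smaller. The complete-at-all-times set mainly wastes data. Its bias is conditional on completeness following the course of pain, which the Discussion's remark on attendance makes plausible but does not establish.

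**What to change.** In the Statistical Analysis section:

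1. Name the multilevel repeated-measures model as the primary analysis, fitted to all observed follow-up values with baseline score as a covariate and no filled values. It is valid if data are missing at random given the observed scores and covariates.
2. Delete LOCF, and do not use the complete-at-all-times set as the main handling.
3. Add one sensitivity analysis, for example multilevel multiple imputation with arm-specific departures from missing at random. This also brings in patients with baseline data only, whom the primary model cannot use.

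The cost is a change of wording and a little more programming. The sample size stays at 932, which already allows for 20% dropout.

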**Methods/Design:**

A Cluster randomised clinical trial will be conducted in 38 Primary Health Care Centres located in Barcelona, Spain and its surrounding areas. The centres are randomly allocated to the multidisciplinary intervention or to usual clinical care. Patients between 18 and 65 years old (n = 932; 466 per arm) and with a diagnostic of a non-specific sub-acute low back pain are included. Patients in the intervention group are receiving the recommendations of clinical practice guidelines, in addition to a biopsychosocial multidisciplinary intervention consisting of group educational sessions lasting a total of 10 hours. The main outcome is change in the score in the Roland Morris disability questionnaire at three months after onset of pain. Other outcomes are severity of pain, quality of life, duration of current non-specific low back pain episode, work sick leave and duration, Fear Avoidance Beliefs and Goldberg Questionnaires. Outcomes will be assessed at baseline, 3, 6 and 12 months. Analysis will be by intention to treat. The intervention effect will be assessed through the standard error of measurement and the effect-size. Responsiveness of each scale will be evaluated by standardised response mean and receiver-operating characteristic method. Recovery according to the patient will be used as an external criterion. A multilevel regression will be performed on repeated measures. The time until the current episode of low back pain takes to subside will be analysed by Cox regression.

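### The protocol article contradicts itself on the primary endpoint: RDQ change at 3 months alone in some places, three questionnaires or three time points in others, with no hierarchy

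*Protocol article*

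**What the plan says.** Three places point to one primary endpoint:

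- Abstract, Methods/Design: "The main outcome is change in the score in the Roland Morris disability questionnaire at three months after onset of pain". The next sentence demotes the other scales: "Other outcomes are severity of pain, quality of life".
- Outcomes, within the first bullet: "The primary outcome is change in the score on the Roland and Morris disability questionnaire at three months after onset of pain".
- Sample size: "The sample-size calculation is based on change in RDQ at three months after onset of LBP".

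Two places point to several:

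- Outcomes opens its list with "Primary outcomes are" and places RDQ, the McGill Pain Questionnaire and SF-12 under it. The secondary list starts only after SF-12.
- Statistical Analysis: "The primary end points for the trial will be 3 months (short term), 6 months and 12 months (long term".

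On error rates, Statistical Analysis says "The significance level of all models will be set at 5" per cent. It plans a multilevel repeated-measures model for each outcome scale. The article gives no hierarchy, split of alpha or rule for trial success. The main objective in Background joins disability, pain, quality of life and incidence of chronic low back pain without ranking them, so it does not settle the question.

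**The concern.** Pain and quality of life are non-primary in the abstract and primary in Outcomes. Six and 12 months are outside the primary endpoint in the abstract, Outcomes and Sample size, and inside it in Statistical Analysis. A reader cannot tell which text governs.

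The error rate and the power behind a claim of effectiveness depend on the answer. On the plural text, a significant SF-12 result at 12 months could be reported as a primary finding even if RDQ at 3 months showed nothing. No power is stated for that comparison, and nothing would limit the overall chance of a false positive. The choice of which primary to emphasise could also be made after the results are known.

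This is more than detail that an article leaves to an analysis plan. A later plan could add a testing order, but it could not make these sections agree.

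**Working it through.** **1. Reproduce the plan's own figure.** Inputs from Sample size: difference 2.5, SD 5.7, alpha 0.05, power 0.90, intraclass correlation 0.1, 25 patients per centre, 20% dropout. Sidedness is not stated; two-sided is taken here.

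- Per arm before clustering: 2 × [5.7 × (1.960 + 1.282) / 2.5]² = 109.24.
- Design effect: 1 + (25 − 1) × 0.1 = 3.4, so 109.24 × 3.4 = 371.4.
- Dropout: 371.4 / 0.80 = 464.3, or 465 per arm and 930 in total.
- Rounding up to 110 first gives 110 × 3.4 / 0.80 = 467.5, or 468 per arm.

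The stated 466 per arm (932) lies between the two. A one-sided test would give 379 per arm, which does not match, so the plan evidently used a two-sided 5% test.

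Power at 466 per arm: 466 × 0.80 / 3.4 = 109.6 effective patients per arm. The standard error is 5.7 × √(2/109.6) = 0.770, and 2.5 / 0.770 − 1.960 = 1.29, which gives power of 90.1%. The calculation is sound, for RDQ at 3 months at the full 5%.

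**2. Count the tests under each reading.**

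- Abstract, Sample size and the singular sentence in Outcomes: 1 test.
- Outcomes list alone (three questionnaires at one time), or the time-point sentence alone (RDQ at three times): 3 tests.
- Both combined: 3 × 3 = 9 tests.

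**3. Chance of at least one false positive, each test at two-sided 5%.** For independent tests this is 1 − 0.95^k:

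- k = 1: 5%
- k = 3: 1 − 0.857 = 14.3%
- k = 9: 1 − 0.630 = 37.0%

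The endpoints are measured in the same patients, so independence is an upper benchmark. With equally correlated normal test statistics (simulated, 400,000 draws):

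| Assumed correlation | 3 tests | 9 tests |
|---|---|---|
| 0 | 14.3% | 37.0% |
| 0.3 | 13.6% | 33% |
| 0.5 | 12.5% | 27% |
| 0.7 | 10.9% | 20% |
| 0.9 | 8.3% | 12% |

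The correlations are assumptions. In every multi-test row the rate exceeds 5%.

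**The case against.** The strongest reply is that the intended primary endpoint is clear. The abstract, the sample size and a singular sentence inside the Outcomes list itself agree on measure and time. On that reading there is one test at 5% with 90% power, and the rest is loose labelling. The time-point sentence in Statistical Analysis names no outcome and may mean only the assessment times. The 5% sentence sits in a paragraph about interactions and collinearity and sets a nominal level; it is not a success rule. The details of multiplicity handling for further outcomes may properly sit in an analysis plan that is not shown.

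Much of this stands, and it limits the point in three ways.

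- A reader might infer that the trial has no error control at all. The document does not support that: error is controlled if RDQ at 3 months is the sole primary. No sentence crosses the three questionnaires with the three times, and none says that success on any one is enough.
- A reader might count components. Of McGill the article says "It assesses 3 parameters: Total Intensity score, Current Intensity score and Visual Analogical Scale (VAS", and SF-12 has eight dimensions, so 1 + 3 + 8 = 12 scores at three times would make 36 tests. The text presents these as scoring and does not make each a separate primary test. Since the models are repeated-measures models per scale, even nine separate tests is not the only reading.
- A reader might infer that the trial is underpowered because alpha would have to be divided. No section proposes such a split, and the remedy below does not need one.

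The reply does not remove the contradiction. Pain and quality of life cannot be both primary and non-primary, and 6 and 12 months cannot be both inside and outside the primary endpoint.

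**Conclusion.** The article is internally inconsistent on its primary endpoint, and the consequence depends on which text governs. If RDQ change at 3 months is the sole primary, the 5% error, the 90% power and the 932 patients all hold. If the plural lists govern, family-wise error is uncontrolled: about 8% to 14% for three tests and 12% to 37% for nine, over assumed correlations from 0.9 down to 0. These figures also assume that a significant result on any listed primary would be claimed as a primary success, which the text permits but does not state. The nine-test family is assembled from two sections. The sample-size arithmetic is not in question.

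**What to change.** - In Outcomes and Statistical Analysis, name one primary endpoint: the between-arm difference in RDQ change at 3 months, estimated from the multilevel model and tested at two-sided 5%.
- Relabel McGill pain, SF-12 and all 6- and 12-month results as secondary, and report them as supportive with confidence intervals.
- Reword the 5% sentence so that the confirmatory level applies to the primary test only.

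The cost is a few sentences, with no change to patients, data collection, sample size or stated power. The change should be made before outcome results are known, because afterwards it no longer protects against choosing the endpoint that succeeded.
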